#### Early termination criteria

2.3.5

The study team may terminate the trial early if continuing the prospective comparative observational study is deemed inappropriate. Early termination may be implemented to ensure participant safety, maintain data integrity, and uphold ethical and administrative feasibility. The following conditions may justify early termination:

*Safety-related reasons*: When a serious safety concern related to the procedure or study process arises, and participant protection can no longer be guaranteed.*Protocol or ethical violations*: When the study site or research team significantly violates the approved protocol, IRB requirements, applicable regulations, or ethical standards, making the continuation of the study inappropriate.*Administrative or operational reasons*: When the continuation of a study becomes substantially infeasible due to institutional administrative decisions, operational challenges, inability to secure necessary resources, or similar limitations.

In the event of early termination, the principal investigator will compile all data collected up to that point, including CRFs and related documents, and submit a summary report to the IRB and the institution. All study documents and collected data will be retained or disposed of in accordance with institutional policies and IRB guidelines.

#### Management of early termination and dropout

2.3.6

In cases of early termination or participant dropout during the study, the investigator will document the reason and timing of withdrawal in both the CRF and the participant’s medical record. If the withdrawal is suspected to be related to an adverse event, follow-up contact will be made to assess the participant’s clinical status. When an adverse event is confirmed, appropriate medical care will be provided in accordance with the clinical guidelines of each participating institution.

If the study is terminated prematurely at either the institutional or overall study level, the principal investigator will compile all collected study materials—including participant records and study documents—up to the point of termination and report them to the IRB and the relevant institution. All data and materials will then be stored or disposed of in accordance with institutional policies and IRB requirements.

Participants who discontinue the study will not be re-enrolled. The inclusion of data collected prior to withdrawal in the final analysis will be determined according to the study protocol and the predefined statistical analysis plan. Since the follow-up assessment at 24–36 h is considered an additional exploratory endpoint, the absence of follow-up data alone will not be classified as dropout. Non-responses at this time point will be treated as missing data and handled accordingly in the analysis.

#### Participant recruitment plan

2.3.7

Participant recruitment will take place naturally within the outpatient clinical settings of the participating institutions. Information sheets describing the study will be posted in each clinic to enable patients with acute LBP to voluntarily inquire about or express interest in participation. Additionally, clinicians may introduce the study to eligible patients during routine consultations if they meet the inclusion criteria.

Supplementary recruitment strategies, such as utilizing community bulletin boards or online platforms (e.g., institutional websites or blogs), may also be employed to enhance awareness of the study. All recruitment procedures will strictly adhere to the methods approved by the IRB.

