**Figure 2 fig2:**
[figure not shown]
Comparison of the two magnetized needle types used in this study (26G × 60 mm and 25G × 100 mm).

All four participating clinical sites routinely use both types of needles in daily practice, depending on actual clinical circumstances. For the purpose of comparative analysis, two sites will be designated to contribute only cases treated with short needles, while the other two sites will contribute only cases treated with long needles. This approach represents a site-level data extraction scheme, rather than a randomized allocation process, and is designed to enable comparative analysis of procedures performed in routine clinical practice without modification of standard patient care.

The study procedures consist of three stages: screening, the treatment visit (Visit 1), and post-procedure follow-up at 24 to 36 h. After providing written informed consent, participants undergo screening, during which demographic characteristics and relevant medical history are collected, and eligibility is assessed based on predefined inclusion and exclusion criteria. Participants who meet all eligibility criteria proceed directly to Visit 1, during which the ultrasound-guided pharmacopuncture intervention and all corresponding study assessments are conducted.

During Visit 1, all enrolled participants undergo a single ultrasound-guided PDRN pharmacopuncture procedure following a standardized protocol. Prior to the intervention, baseline assessments are conducted, including Numerical Rating Scale (NRS) scores for LBP and radiating leg pain, lumbar ROM, the Oswestry Disability Index (ODI), and the Patient-reported Percentage Pain Reduction(PRPPR) score. After the baseline evaluation, the practitioner identifies the interfascial QPI space using high-resolution ultrasonography and then performs the injection using a magnetically guided needle system, administering 1–2 mL of the PDRN pharmacopuncture solution.

The procedure is performed using an in-plane needle approach, enabling real-time visualization of the needle trajectory and tip through ultrasound imaging combined with a magnetic needle-tracking system. Both groups receive the same injection technique and target the same anatomical site; however, the SNG uses a 26G × 60 mm needle, while the LNG uses a 25G × 100 mm needle. All other procedural variables remain consistent across groups.

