#### Exclusion criteria

2.3.3

Participants will be excluded if any of the following apply:Participants who have received medication or related treatments for LBP or discomfort within the past 7 days, including treatment at medical (Western medicine) or Korean medicine institutions.Participants with a history of lumbar spine surgery within the past 3 months.Participants who developed lumbar sprain due to trauma (e.g., traffic accident, fall, or contusion) within the past 3 months.Female Participants who are currently pregnant or who have given birth within the past 6 months.Participants with renal or endocrine disorders accompanied by symptoms such as edema.Participants currently taking antithrombotic agents (including anticoagulants or antiplatelet medications).Participants with cognitive impairment that makes it difficult to understand the study procedures or provide voluntary informed consent.Participants currently taking psychiatric medications for conditions such as depression.Participants deemed unsuitable for participation at the discretion of the investigator (e.g., refusal to follow instructions, safety concerns).

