Despite these strengths, this study has several inherent limitations due to its exploratory observational design. First, the site-based allocation approach may introduce selection bias. Second, because the intervention was conducted as a single session with short-term follow-up (24–36 h), the study design does not permit evaluation of sustained or cumulative treatment effects. Third, not all participants underwent imaging-based diagnostic confirmation, which may lead to diagnostic heterogeneity and should be taken into account when interpreting the findings.

Future research should include randomized controlled trials to verify the independent effects of needle length and NGS application, as well as quantitative imaging-based assessments of needle tip visibility and tracking accuracy. Additionally, studies incorporating repeated interventions, long-term follow-up, and subgroup analyses based on BMI, muscle thickness, or pain phenotype may further clarify patient-specific treatment responses. Finally, cost-effectiveness analyses would help determine the practical value of ultrasound-guided interfascial pharmacopuncture in primary care settings and contribute to establishing clearer clinical indications and standardized application criteria for the QPI-guided approach.

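### Clinicians may choose whom to invite, and advertising may differ by clinic, although each clinic supplies only one needle, so the two groups can be selected differently

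*Protocol article*

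**What the plan says.** Section 2.3.7 describes three recruitment routes.

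- The first is self-referral in the clinic (the quote stops one word short of the sentence's end): "Information sheets describing the study will be posted in each clinic to enable patients with acute LBP to voluntarily inquire about or express interest in".
- The second is the clinician: "clinicians may introduce the study to eligible patients during routine consultations if they meet the inclusion criteria".
- The third is optional publicity: "utilizing community bulletin boards or online platforms (e.g., institutional websites or blogs), may also be employed to enhance awareness of the study".

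The second and third are worded as permissions. The section does not call for consecutive invitation or for the same mix of routes at each clinic.

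The group is fixed by the clinic. Section 2.1 assigns needle types to sites (the quote again stops one word short): "two sites will be designated to contribute only cases treated with short needles, while the other two sites will contribute only cases treated with long". The last inclusion criterion (section 2.3.2) ties each named clinic to its needle. Outside the study the needle is not fixed: "All four participating clinical sites routinely use both types of needles in daily practice, depending on actual clinical circumstances".

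Section 2.3.8 starts registration after written consent and assesses eligibility after that. The Discussion concedes that "the site-based allocation approach may introduce selection bias" and does not mention the invitation step.

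**The concern.** In a randomised trial, selective invitation limits who the result applies to but leaves the comparison intact, because assignment comes afterwards. Here assignment comes first. A clinician at a short-needle clinic and one at a long-needle clinic each decide whether to raise the study, knowing which needle the patient's data will represent. If they decide differently, the groups differ before any treatment effect.

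The article itself supplies a plausible reason for them to differ. The Introduction and the Discussion both say that needles of about 60 mm may not reliably reach the target. The Discussion links this to thicker soft tissue and puts the target at about 4 to 6 cm or deeper. A clinician whose site contributes only short-needle cases could thus hesitate to mention the study to a larger patient, where a colleague at a long-needle site would not. Optional advertising adds a second way for clinics, and so needles, to attract different patients.

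At stake is the primary comparison, the between-group difference in immediate change in NRS. Selection could create a difference or hide one.

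**Working it through.** **The passages side by side.** Section 2.3.7 permits clinician invitation and extra publicity. Sections 2.1 and 2.3.2 make clinic and needle the same thing within the study. Together, any difference between clinics in whom they invite or attract is a difference between needle groups. The clinician's judgement that a patient qualifies comes before invitation (2.3.7). The formal eligibility check comes after consent (2.3.8), so the earlier judgement lies outside the described registration process.

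**What adjustment can reach.** Table 1 and section 2.1 show that height, weight, NRS and ODI are recorded at baseline. Section 2.6.2 allows ANCOVA or regression, but only if baseline differences are significant and judged relevant. Selection on build or baseline pain is therefore adjustable in principle among participants. Selection on an impression that no one records is not.

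**The plan's own figure.** The inputs from section 2.6.1 are d = 0.56, two-sample t-test, alpha 0.05 and power 80%. The test is two-sided (section 2.6.2). The exact t-test calculation gives 51.03 per group, rounded up to 52, or 104 in total, with power 0.807. The stated 104 reproduces. With 10% dropout, 104 / 0.90 = 115.6, so 116; the stated 120 is slightly more generous. Power at 60 per group is 0.860.

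**Scale.** The trial used for sizing had mean reductions of 2.74 and 1.76 points, so the implied SD is (2.74 − 1.76) / 0.56 = 1.75 points.

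**Assumed shift.** Suppose a share p of one group's eligible patients is not invited and would have had g points less relief than those invited. That group's mean is then too high by p × g. The comparison is biased by the difference of this product between groups, and equal selection cancels. The documents give neither p nor g, so the shift is varied as an assumption. With no true needle effect and a shift of b SD, the chance of p < 0.05 is the power of the t-test at effect size b (noncentrality b × √(n/2), 2n − 2 degrees of freedom):

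| Shift (SD) | Shift (points, × 1.75) | 52 per group | 60 per group |
|---|---|---|---|
| 0 | 0 | 5% | 5% |
| 0.1 | 0.18 | 8.0% | 8.4% |
| 0.2 | 0.35 | 17.3% | 19.2% |
| 0.3 | 0.53 | 32.9% | 37.1% |
| 0.4 | 0.70 | 52.4% | 58.4% |

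A larger sample makes the error more likely, because the bias stays while the standard error shrinks.

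**What such shifts would need.** Suppose selection acts in one group only and g = 1.5 points (also an assumption). A shift of 0.1 SD (0.175 points) needs 0.175 / 1.5 = 12% of eligible patients passed over. A shift of 0.4 SD (0.70 points) needs 0.70 / 1.5 = 47%. The top of the range is therefore demanding.

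**The other direction.** If a true difference of 0.56 SD were offset by 0.16 SD, 0.40 SD would remain, and power at 60 per group would fall from 86.0% to 58.4%.

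**The case against.** The best case on the other side has several parts.

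- **Posted sheets.** They come first in section 2.3.7 and are planned at every clinic; the clinician route is an addition. A reader might infer that entry rests with clinicians alone. The text does not support that.
- **Records.** A reader might infer that no one will know who was passed over. The article mentions no screening log, but it does not say that none is kept, and a condensed article commonly leaves this to the full protocol. The point therefore rests on the permissive rule that is stated.
- **Adjustment.** A reader might infer that adjustment cannot help. For build and baseline pain, the factors that a clinician most obviously sees, it partly can. What remains is selection on unrecorded factors, and the fact that adjustment depends on a significance test.
- **Discretionary exclusion.** Section 2.3.3 removes "Participants deemed unsuitable for participation at the discretion of the investigator". Under section 2.3.8 eligibility is assessed after consent, so this is a different step and does not support the point.
- **Concession and status.** The Discussion admits selection bias, and the study calls itself exploratory. But the admission concerns site allocation, and it does not reduce a bias that a change of wording could reduce before enrolment.
- **No evidence of differential selection.** This is correct. Selection alike in both groups would not bias the contrast, and the documents show neither its size nor its direction.

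**Conclusion.** The point holds in a limited form. The stated rule makes clinician invitation optional and lets publicity vary by clinic in a design where clinic determines needle. Differential invitation can therefore bias the comparison, and neither the conceded limitation nor the conditional adjustment deals with the invitation step.

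It does not follow that the groups will be selected differently, or that such selection would go unrecorded. The range of about 8% to 58% for the false-positive rate at 60 per group rests wholly on the assumed shift of 0.1 to 0.4 SD. It also rests on an SD of 1.75 taken from a 3-week chronic-pain trial, which may not match the spread of an immediate change in acute pain. No sample-size figure needs to change. The correction is worth making because the article reports that no participant had been recruited at submission.

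**What to change.** Replace the permissive sentence in section 2.3.7 with a rule on these lines: *Every consecutive eligible patient with acute low back pain is invited, using the same recruitment routes at all four clinics.*

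Add two reporting items:

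- Record the recruitment route for each participant.
- Report, by needle group, anonymous counts per clinic of patients eligible, invited, declined, and not enrolled with the reason. Treatment with the other needle should be one of the reasons, because the last inclusion criterion removes those patients and an invitation rule alone would not show them.

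The counts should stay anonymous and within what the IRB approves. Sections 2.3 and 2.3.8 put consent before study procedures and registration, so a log of individual data on people who have not consented would conflict with them.

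The cost is a few minutes of existing staff time per patient and minor IRB handling. Patient care and the sample size stay as they are.

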#### Registration of participants

2.3.8

Individuals expressing interest in participating will be provided with detailed information about the study’s objectives, procedures, potential benefits and risks, and data privacy protections. The registration process will begin only after participants voluntarily sign the written informed consent form.

Following consent, eligibility will be assessed based on predefined inclusion and exclusion criteria. Participants who meet all criteria will be formally enrolled in the study, and baseline assessments and the intervention will be conducted during the first visit (Visit 1). All procedure-related clinical information and evaluation outcomes will be systematically recorded using a standardized CRF.

### Intervention

2.4

All procedures in this study will be performed under real-time ultrasound guidance using a portable ultrasound system equipped with a magnetic needle-tracking function (AcuViz Pocket, FCU Corp., Korea). This device incorporates a magnetic sensor system that detects the position and trajectory of magnetized needles and displays them in real time on the ultrasound screen via a Needle Guiding System (NGS), thereby enhancing needle visibility during insertion.

Two types of magnetized needles will be used depending on group allocation. The Acu-tracking needle (26G × 60 mm; YONG CHANG Co., LTD., Korea) will be used for procedures in the SNG, while the Ez-tracking needle (25G × 100 mm; YONG CHANG Co., LTD., Korea) will be used for the LNG.

The pharmacopuncture solution used in this study is a salmon (Oncorhynchus spp.)-derived PDRN formulation. A 2 mL vial of PDRN pharmacopuncture solution (Yeona Pharmacopuncture; AJ External Herbal Dispensing Facility, Seoul, Republic of Korea), an MOHW-certified compounding facility, will be used for all procedures. PDRN consists of purified DNA polymer fragments (Polynucleotides) and has been reported to exert anti-inflammatory effects, promote tissue regeneration, improve microcirculation, and reduce pain (14). Accordingly, PDRN-based pharmacopuncture has been clinically utilized for lumbar pain, spinal stenosis, and radicular symptoms (15–17).

For administration, the solution will be aspirated into a 3 cc disposable syringe (Sungshim Medical Co., Republic of Korea) using an attached sterile needle. The needle will then be replaced with either the Acu-tracking needle or the Ez-tracking needle, according to group assignment, before injection.

#### Ultrasound-guided interfascial injection procedure at the QPI space

2.4.1

The L3 spinous process is initially identified using an ultrasound device (AcuViz Pocket).The probe is then rotated 90 degrees to obtain a transverse view and visualize the transverse process of L3.The probe is moved slightly cranially until the PM, previously obscured by the transverse process, becomes visible.The probe is adjusted until the medial border of the QL aligns approximately with the lateral border of the IC muscle.After identifying the IC, QL, and PM muscles, the probe is stabilized once a peristaltic bowel movement is observed lateral to the PM, indicating the appropriate depth and confirming the anatomical landmarks.The skin over the planned needle entry site is thoroughly disinfected over a sufficiently wide area.Using an in-plane approach, the magnetic pharmacopuncture needle is advanced toward the medial border of the QL muscle and positioned within the interfascial plane. The injectate is then slowly administered to facilitate natural spread toward the PM fascia.During the procedure, the patient may experience transient neural sensations, such as radiating tingling, warmth, numbness, or a relieving sensation in the lower limb.After completing the injection, the needle is withdrawn, and hemostasis is achieved if bleeding occurs, followed by the application of a sterile dressing.The patient is instructed to stand and perform gentle lumbar flexion, extension, and rotation to assess any changes in symptoms or adverse reactions (Figure 3).

**Figure 3 fig3:**
[figure not shown]
Ultrasound-guided pharmacopuncture procedure and post-treatment process in the QPI space. **(A)** Identification of the transverse process of the third lumbar vertebra (L3) and the iliocostalis, psoas major, and quadratus lumborum muscles using ultrasound imaging. **(B)** After skin disinfection at the needle insertion site, the needle is advanced using an in-plane ultrasound-guided approach, and pharmacopuncture solution is injected into the QPI interfascial space. **(C,D)** Upon completion of the injection, the needle is withdrawn, hemostasis is performed if bleeding occurs, and a sterile dressing is applied. **(E,F)** Mild lumbar flexion, extension, and rotation are performed to assess symptom changes and to monitor for any immediate adverse reactions. The model depicted in this figure is one of the investigators participating in this study and provided prior consent for the use of the photograph in the publication.

### Outcomes

2.5

#### Primary outcome

2.5.1

The primary outcome of this study is the change in Numeric Rating Scale (NRS) scores for LBP immediately following ultrasound-guided pharmacopuncture.

The NRS score recorded immediately before the procedure will serve as the baseline, and a second NRS assessment will be conducted immediately after the intervention (QPI-guided PDRN pharmacopuncture). The difference between the baseline and post-procedure scores will be calculated to determine the extent of symptom improvement. A between-group comparison of NRS changes (SNG versus LNG) will be used to evaluate whether needle length influences the magnitude of acute pain reduction.

#### Secondary outcomes

2.5.2

##### Change in lumbar ROM

2.5.2.1

Lumbar ROM (flexion, extension, lateral flexion, and rotation) will be assessed immediately before the procedure and reassessed immediately afterward. The change from baseline (ΔROM) will be calculated to evaluate the short-term functional improvement associated with needle length. Between-group differences in ΔROM will be analyzed to determine whether long needles provide greater mobility gains compared to short needles.

Lumbar ROM will be measured using a standard goniometer. Flexion and extension will be assessed in a standing position, with the axis placed lateral to the lumbosacral joint, the stationary arm aligned vertically, and the moving arm aligned with the lateral trunk line. Lateral flexion will be measured from the posterior aspect, with the axis positioned over the midline of the lumbosacral junction, the stationary arm parallel to the line connecting the posterior superior iliac spines (PSIS), and the moving arm directed along the spinous processes toward C7. Rotation will be measured in a seated position, with the axis located at the cranial midline, the stationary arm parallel to the floor, and the moving arm directed toward the contralateral acromion (18).

